## Abstract

**Background:**

Evidence suggests a strong association between nutrition during the first 1000 days (conception to 2 years of life) and cognitive development. Maternal docosahexaenoic acid (DHA) supplementation has been suggested to be linked with cognitive development of their offspring. DHA is a structural component of human brain and retina, and can be derived from marine algae, fatty fish and marine oils. Since Indian diets are largely devoid of such products, plasma DHA levels are low. We are testing the effect of pre- and post-natal DHA maternal supplementation in India on infant motor and mental development, anthropometry and morbidity patterns.

**Methods:**

DHANI is a double-blinded, parallel group, randomized, placebo controlled trial supplementing 957 pregnant women aged 18–35 years from ≤20 weeks gestation through 6 months postpartum with 400 mg/d algal-derived DHA or placebo. Data on the participant’s socio-demographic profile, anthropometric measurements and dietary intake are being recorded at baseline. The mother-infant dyads are followed through age 12 months. The primary outcome variable is infant motor and mental development quotient at 12 months of age evaluated by Development Assessment Scale in Indian Infants (DASII). Secondary outcomes are gestational age, APGAR scores, and infant anthropometry. Biochemical indices (blood and breast-milk) from mother-child dyads are being collected to estimate changes in DHA levels in response to supplementation.

All analyses will follow the intent-to-treat principle. Two-sample t test will be used to test unadjusted difference in mean DASII score between placebo and DHA group. Adjusted analyses will be performed using multiple linear regression.

**Discussion:**

Implications for maternal and child health and nutrition in India: DHANI is the first large pre- and post-natal maternal dietary supplementation trial in India. If the trial finds substantial benefit, it can serve as a learning to scale up the DHA intervention in the country.

**Trial registration:**

The trial is retrospectively registered at clinicaltrials.gov (NCT01580345, NCT03072277) and ctri.nic.in (CTRI/2013/04/003540, CTRI/2017/08/009296).

## Background

The period from conception through to a child’s second birthday, commonly referred to as ‘the first 1000 days’, is a crucial window to improve maternal child health and nutrition indicators and optimize human capital [1, 2]. The brain develops rapidly through neurogenesis, axonal and dendritic growth, synaptogenesis, cell death, synaptic pruning, myelination, and gliogenesis [3–5]. These ontogenetic events build on each other, such that even small perturbations can have long-term effects on the brain’s structural and functional capacity [6]. A mother’s nutrition during this critical phase impacts both prenatal and postnatal growth and the development of offspring [7, 8]. Higher omega 3 long chain poly unsaturated fatty acid (n-3 LCPUFA) levels such as docosahexaenoic acid (DHA) have been associated with enhanced infant neurodevelopment [9–16].

DHA is an important structural component of human brain and retina. It can be obtained from marine algae, fatty fish and marine oils. Since Indian diets are largely deficient in DHA-rich sources, the population levels of plasma DHA are quite low [17, 18]. Indians do consume sources of the precursor, alpha-linolenic acid (ALNA 18:3n-3; a short-chain omega-3 fatty acid) like mustard oil, soybean oil, flaxseeds, walnuts. However, excess omega-6 fats in Indian diets inhibit the endogenous synthesis of DHA from ALNA [19]. Thus, negligible DHA-rich products coupled with an excess of omega-6 sources result in low plasma DHA and a sub-optimal omega-3 to omega-6 ratio among Indian populations [20, 21]. The ideal ratio of omega-3 to omega-6 should be 1:1 to 1:2.5. However, in Indian diets it is usually around 1:17 to 1:20 [22, 23]. These low levels become a concern especially during peak spurts of neurodevelopment such as the first 1000 days [24].

### DHA and neurodevelopment

Long chain polyunsaturated fatty acids, particularly DHA (22:6n-3) and arachidonic acid (20:4n-6), are integral to fetal, neural and retinal development and accrete extensively in the last trimester of pregnancy [25]. Despite the implications for child development, there have been few studies which have comprehensively tested interventions in humans. Makrides et al. showed that high-DHA (approximately 1% total fatty acids) enteral feeds compared with standard DHA (approximately 0.3% total fatty acids) from day 2 to 4 of postnatal life showed significantly higher (unadjusted mean difference, 4.7; 95% CI, 0.5–8.8; adjusted mean difference, 4.5; 95% CI, 0.5–8.5) Bayley’s Mental Development Index scores in Australian girls, however among the boys, it did not differ between groups [26, 27]. Ramakrishnan et al. [28] summarized studies in this area and reported that observational studies indicated a direct association between poor n–3 fatty acid status and increased risk of maternal depression and childhood behavioral disorders such as attention-deficit hyperactivity disorder (ADHD). It has also been hypothesized that prenatal exposure to DHA may also affect later development through fetal programming of the central nervous system and various other physiologic pathways. Ramakrishnan et al. in 2016 reported a beneficial impact of prenatal DHA supplementation on attention in preschoolers at 5 years of age where DHA group children recorded significantly fewer omissions (< 40) as compared to the control group on K-CPT (Conners’ Kiddie Continuous Performance Test). Also, the magnitude of positive association between home stimulation and cognitive functioning was found to be less in the DHA group (b = 0.71; 95% CI: 0.13, 1.29; placebo group: b = 1.71; 95% CI: 1.09), [29]. Another randomized trial, the DHA Intake and Measurement of Neural Development (DIAMOND) study [16] suggested some benefit of DHA supplementation of infants form 1–9 days of age till 12 months on visual acuity of infants at 1 year of age. It was observed that infants fed with control formula had significantly poorer visual acuity than the infants who were fed with DHA-supplemented formulas (*P* < 0.001). Evidence for association between increased consumption of sea food in pregnancy and improved neurodevelopmental outcomes in their children have also been shown in observational studies [30–33]. However, evidence from intervention trials from low- and middle-income settings is scanty. Most of the studies reviewed were conducted in developed countries. Some trials had small sample sizes too. Thus large, well-designed, community-based prevention trials from developing countries are warranted.

In summary, studies conducted to date suggest that improvements in DHA levels in mother may confer some benefit for child neurodevelopment. Furthermore, DHA appears to be safe, with no adverse birth outcomes related to DHA supplementation observed in low- risk pregnancy cases [34]. Very few studies to date have continued supplementation through lactation. We therefore implemented a large scale randomized trial to study the effects of pre- and post-natal DHA supplementation on birth weight, gestational age and neurodevelopment in India, a country with low DHA intakes and a high dietary n-6 to n-3 ratio. This will be the first to examine the effects of in-utero and early life DHA exposure (through maternal supplementation from mid-pregnancy through 6 months postpartum) on postnatal neurodevelopment and body-size of Indian infants. Long term contact and follow-up with this cohort is being planned. The biological specimens being collected (blood, cord-blood, and breast-milk) from the mother-child dyads can further help pursue new hypotheses and unravel critical information about early DHA intervention on later life of an individual [35–41].

## Methods

### Study design

DocosaHexaenoic Acid supplementation during pregnancy and lactation on Neurodevelopment of the offspring in India (DHANI) is a double-blinded, randomized, placebo controlled trial being conducted in India. Study participants are healthy pregnant women and their offsprings.

DHANI will assess the impact of 400 mg of pre- and post-natal DHA supplementation (from ≤20 weeks of gestation to 6 months postpartum) on infant neurodevelopment at 6 and 12 months as measured by the Development Assessment Scale for Indian Infants (DASII). Secondary objectives of this trial include an assessment of the impact of maternal DHA supplementation on: gestational age, new born anthropometry (birth weight, length and head circumference) and APGAR score; infant anthropometry (birth weight, length and head circumference) at birth, 1 month, 6 months and 12 months; number of unfavorable pregnancy outcomes (still births, low birth weight babies, preterm babies); morbidity patterns through 12 months in the two groups. The first mother was enrolled on 6 Jan 2016 and the last on 31st Aug 2017. The data being collected under the trial for mother-infant dyads at each time point has been presented in Table 1.

**Table 1 Tab1:** Data being collected under DHANI trial

Domain	Measure	Data obtained on woman						Data obtained on child		
		Pregnancy		Delivery	Post partum/ lactation			Birth	6 months	12 months
		Enrolment at < =20 weeks	Each month until Delivery	Delivery	2-3rd Day Post partum	1 month Post partum	6 month post partum			
Socio-economic and demographic profile	Demographics	X								
	family details	X								
	Income	X								
	Education	X								
	Occupation	X								
Medical and Obstetric History	Clinical Investigation	X	X	X	X		X	X	X	X
	Obstetric History	X								
	Complications	X	X	X	X	X	X	X	X	X
	Adverse events	X	X	X	X	X	X	X	X	X
	Eligibility	X								
Blood	Fatty acid composition	X		X			X	X	X	X
Breast milk (30%)	Fatty acid composition				X	X	X			
Body Size & composition	Anthropometry (weight, length, mid upper arm circumference, head circumference of offspring)	X	X	X	X	X	X	X	X	X
Behavioral Factors	Dietary Intake	X							X	X
	Physical activity	X					X			
	Prenatal Care	X	X							
	Substance use	X								
Child development	APGAR							X		
	Developmental Quotient								X	X
	Morbidity	X	X	X	X	X	X	X	X	X

### Study population

The study population consists of 18–35 year old women with singleton pregnancy of ≤20 weeks of gestational age registered at the Obstetrics and Gynaecology outpatient department (OBGYN OPD), Prabhakar Kore hospital (PKH) for antenatal check-up. The PKH under KLE University’s Jawaharlal Nehru Medical College (JNMC) in Belgavi, Karnataka, India caters to the local population and the villages in and around Belgavi. PKH reports nearly 500–600 deliveries per month. Detailed inclusion and exclusion criteria are provided in Table 2.

**Table 2 Tab2:** Inclusion and Exclusion Criteria for DHANI trial

Inclusion Criteria:	Exclusion Criteria:
• Pregnant woman aged 18 years to 35 years (singleton) at ≤20 weeks of gestation (calculated from the last menstrual period or by ultrasound in 1st trimester as suggested by study physician/team). • Willing to participate in the study and provide all measurement for self, husband and the offspring including anthropometry, dietary assessment and questionnaire plus the biological samples (blood, breast milk) • Willing to provide signed and dated written informed consent. • Plans to deliver at the study hospital • Willing to comply with study specific procedure/instruction	• Women with high-risk pregnancies or bad obstetric history • Women with chronic conditions like Hypertension, heart disease, Cancer, Diabetes, epilepsy, liver disorders, thyroid problem, known history of bleeding disorders or thrombosis or any other medical condition which may affect the safety of mother/infant in opinion of study investigator/physician. • Women allergic (if aware) to any of the test products • Women consuming omega-3/DHA supplements or having used these in 3 months preceding the intervention period. • Participated in another drug trial within or before 3 months from the date of screening under this study or during the study

**Table 3 Tab3:** Expected Adverse Events (AE) and Serious Adverse Events (SAE)

Averse Events	Serious Adverse Events
• Preterm labour • Premature rupture of membranes • Preeclampsia • Urinary Infection	• Abortion • Abruptio-placenta • Intra Uterine Death • Fresh Still Birth • Macerated Still Birth • Congenital anomalies • Neonatal death • Maternal Death

### Exposure

The exposure is 400 mg of algal DHA to be consumed daily by pregnant women from ≤20 weeks of gestation until 6 months postpartum recruited under the trial. The study staff delivers a bottle with 35 capsules (2 capsules per day X 15 day + 5 extra for spillage, spoilage, etc.,) which match the allotted code of the subject. The bottles are either collected by the participant every fortnight or distributed by study personnel during fortnightly visits at the participant’s home or workplace. The women are instructed to take two capsules daily, preferably at the same time each day.

### Control

The control is a placebo which contains 200 mg per capsule of corn/soy oil (both active and placebo capsules provide the same, but negligible, energy). The placebo capsules provide no DHA and a negligible amount of omega-6 fatty acids. The active and placebo capsules are identical with respect to taste and appearance and only differ in coding.

### Outcomes

#### Primary outcome

Mean difference in the infant neurodevelopmental score (DQ), motor score and mental scores, as measured by the DASII scale 12 months.

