### Effect size, power and sample size

The primary outcome variables are infant motor and mental development quotient at 12 months of age. The smallest effect sizes of interest were 0.25 S.D. for motor and mental development at 12 months of age [42]. Using a two-tailed test and a significance level of α = 0.05, a final sample of 338 infants per group (676 mother-child dyads) was required at the end of the study (12 months postpartum) to provide 90% power. A total of 957 mothers have been recruited in the present study, allowing for potential attrition due to serious adverse events, withdrawal, and migration out of the study area. Breast-milk samples are being collected within 3–4 days after delivery and at 1 month and 6 months postpartum from a 30% convenience sub-sample - 150 mother-infant pairs per group, which will have 95% power to detect effect sizes of 0.5 S.D. in DHA levels.

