### Data collection

Primary outcome variable: The development quotient (DQ) among infants at 12 months of age assessed using the standardized DASII scale [43, 44] by two trained psychologists is the primary outcome variable [45, 46]. DASII is the Indian modification (done in 1970 and 1977) of the Bayley Scale of Infant Development (BSID) using Indian norms for 67 motor and 163 mental items of the BSID. DASII provides a measure of DQ among Indian infants below 30 months of age [47, 48]. DQ is defined as the ratio of functional to chronological age. Third, 50th and 97th percentile norms are given. The maximum DQ score is 100; ≥85 is normal; 71–84 is mild to moderate delay and developmental delay is defined as DQ ≤70 (≤2SD). Median reliability index for motor and mental scales based on correlation between consecutive months is noted to be 0.88 for motor scales and 0.91 for mental scales. The motor development items cover the child’s development from supine to erect posture, neck-control, locomotion etc. It also includes the record for manipulative behaviour such as reaching, picking-up, handling things etc. The mental development items record the child’s cognizance of objects in the surroundings, perceptual pursuit of moving objects, exploring them to meaningful manipulation. It also covers the development of communication and language comprehension, spatial relationship and manual dexterity, imitative behavior and social interaction etc. Each child undergoes DASII assessment twice – once at 6 months and again at 12 months. For infants born preterm, the assessment is done at their corrected ages of 6 and 12 months.

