### Statistical analyses

All the analyses will be performed on the principle of ‘intention to treat’ unless otherwise specified (i.e., we will compare patients in the groups to which they were originally randomly assigned). Statistical analyses will be performed using STATA Version 14.0. We will summarize maternal and household characteristics in the two groups and assess the effectiveness of randomization by comparing these between the groups. Continuous, normally distributed variables will be summarized as means and standard deviations, while skewed variables will be summarized as medians and inter-quartile ranges. Categorical/binary variables will be summarized using proportions. Comparisons on baseline characteristics will also be made between the final study sample and those who were lost to follow up.

For the primary outcome, we will test the unadjusted difference in the mean DASII score at 6 months and 12 months between the two treatment groups using a two-sample t-test. For adjusted analyses, we will consider the DASII score as a continuous variable and use a multiple linear regression model, adjusting for treatment, sex of the child, maternal age, maternal education, socio economic status, birth-weight and other factors which we find out to be significant at baseline comparison. We will adjust for the 6 month DASII score in the model examining the difference in score at 12 months between the treatment groups using Generalized Estimating Equation (GEE) analyses to account for correlation between the 6 month and 12 month DASII score.

The DASII score will also be analysed as a binary variable. DASII score ≤ 70 will be used to defined developmental delay. The unadjusted and adjusted relative risk in the proportion of DASII score (≤70) at 12 months between DHA and placebo groups will be calculated using a log-binomial regression. In case of convergence issues with the log-binomial model, logistic regressions will be used to conduct the adjusted analyses and adjusted odds ratios will be reported instead of adjusted relative risks.

The differences in weight, length, head circumference, still birth, Apgar score at 1 min & 5 min of the infants at birth will be tested using t-test. Adjusted analyses will be performed using multiple linear regression.

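### The primary outcome is one, two or three DASII scores depending on the section, and is analysed at two ages, while the sample size covers one score at one age at an undivided two-sided 0.05.

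*Protocol article*

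**What the plan says.** **Which scores are primary (protocol article).**

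- Primary outcome section, three scores: "Mean difference in the infant neurodevelopmental score (DQ), motor score and mental scores, as measured by the DASII scale 12 months".
- Effect size, power and sample size, two scores: "The primary outcome variables are infant motor and mental development quotient at 12 months of age". The abstract agrees: "The primary outcome variable is infant motor and mental development quotient at 12 months of age".
- Data collection, one score: "The development quotient (DQ) among infants at 12 months of age assessed using the standardized DASII scale" is there called the primary outcome variable.

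**Which age is primary.** Each of those four places says 12 months. Statistical analyses, however, states: "For the primary outcome, we will test the unadjusted difference in the mean DASII score at 6 months and 12 months". It does not say which DASII score is meant. Study design also puts the main objective at both ages: "on infant neurodevelopment at 6 and 12 months as measured by the Development Assessment Scale for Indian Infants (DASII".

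**Error rate and power.** A significance level is set once, in the sample-size section: "Using a two-tailed test and a significance level of α = 0.05". The effect size there refers to both scores: "The smallest effect sizes of interest were 0.25 S.D. for motor and mental development at 12 months of age". The result is 338 infants per group for 90% power, and 957 women were randomised.

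**The concern.** A confirmatory claim needs a fixed set of comparisons, because the error rate and power belong to that set. Here the set ranges from one comparison (DQ at 12 months) to six (three scores at two ages), depending on the section. The sample-size section itself names two primary variables but plans for one comparison.

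The DASII is given at both ages to every child, so all of these results will exist at the end. If the definition is still open when treatment codes are released, the score or age reported as primary could follow the data. The article also states that registration was completed after recruitment had begun, so the protocol's own wording has to carry the definition.

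**Working it through.** **Inputs from the article:** effect 0.25 SD, two-sided alpha 0.05, power 90%, 338 per group, equal allocation, 957 randomised.

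**Assumptions (the article gives no figures):** motor-mental correlation r from 0 to 0.8; between-age correlation t from 0.3 to 0.7; overall DQ taken as the mean of motor and mental with equal SDs, so that it correlates √((1+r)/2) with each; correlations across both score and age taken as the product of the two.

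**1. The plan's own figure.** The expected test statistic is 0.25/√(2/338) = 3.25. Power at two-sided 0.05 is Φ(3.25 − 1.96) = Φ(1.29) = 0.901. The exact t-test gives 0.9007. The exact n is 337.2, which rounds up to 338. So 338 is correct for one comparison at an undivided 0.05.

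**2. If any significant score counts, each at 0.05.** For independent tests the rate is 1 − 0.95^m: 9.75% for m = 2, 14.3% for m = 3 and 26.5% for m = 6. The scores are related, so I simulated correlated test statistics (1,000,000 draws per setting, critical value 1.96).

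**3. If motor and mental must both succeed.** The false-positive rate stays within 5%. Power at r = 0 is 0.9015² = 0.813, and it rises with r.

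| Motor-mental r | Any of 2 | Any of 3 | Any of 6, t = 0.3 | Any of 6, t = 0.7 | Power for both |
|---|---|---|---|---|---|
| 0 | 9.75% | 11.5% | 21.1% | 18.5% | 81% |
| 0.3 | 9.5% | 10.5% | 19.4% | 17.0% | 82% |
| 0.5 | 9.1% | 9.7% | 18.0% | 15.7% | 83% |
| 0.7 | 8.3% | 8.6% | 16.1% | 14.1% | 85% |
| 0.8 | 7.8% | 8.0% | 14.9% | 13.0% | 86% |

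**4. Two primaries under Holm at overall 0.05.**

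- At the 0.025 first step, power per score is Φ(3.25 − 2.241) = Φ(1.009) = 0.843, or 0.842 by the exact t-test: 84%.
- Holm also accepts a score at 0.05 once the other has passed 0.025. If both true effects are 0.25 SD, simulated power per score at 338 per group is 88-89% for r from 0 to 0.8.
- 90% at the 0.025 step needs an exact n of 398.4, so 399 per group or 798 infants. The 957 randomised supply this if loss is at most 1 − 798/957 = 16.6%. The planned 676 allows 1 − 676/957 = 29.4%.

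**The case against.** Several points on the other side have force.

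- **Separate tests at 0.05 are inferred.** The analysis section gives no significance level. A multiplicity or success rule is commonly left to the analysis plan, which is not shown, so its absence is not the finding. What stands is that the article's own definitions conflict, and that its sample size allows nothing for the second primary variable it names.
- **The age is largely settled.** Every place that defines the primary outcome says 12 months. The analysis section mentions 6 months under the primary outcome, but the same paragraph then uses the 6-month score as an adjustment in the 12-month model. A reader might infer six primary tests and a fourfold error rate. That is the worst-case reading, not something the article states.
- **The single DQ may be an umbrella term.** Data collection goes on to describe the motor and mental scales, so its DQ could stand for both quotients. The firm conflict is three scores in the Primary outcome section against two in the sample-size section.
- **The two harms need opposite rules.** A reader might infer that the trial has both an inflated error rate and too little power. It cannot have both. Under an any-score rule, the chance of at least one win on motor or mental is 94-99%. Under a both-scores rule, error is controlled.
- **Strong correlation shrinks the effect.** At r = 0.8 the two-score rate is 7.8%, about 1.6 times the nominal level. It still exceeds 5%.

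**Conclusion.** The concern holds as an inconsistency in the definition of the primary outcome, and it affects what the trial may claim. The sections disagree on the number of primary scores, and the analysis section adds a second age. The 338 per group is arithmetically right, but 5% and 90% hold together only for one score at one age.

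Under the assumed correlations, an any-score rule gives a false-positive rate of about 8-10% (two scores), 8-11.5% (three) or 13-21% (six, worst case). A both-scores rule instead gives 81-86% power at 338 per group. The article adopts neither rule, so these ranges show what the open definition permits and not what the trial's error rate or power is. It would go too far to say that the stated 5% and 90% are wrong: with one score named at 12 months, both are correct.

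**What to change.** Before the analysis team is unblinded, make the abstract, Primary outcome, sample-size, Data collection and Statistical analyses sections agree. Set 12 months as the only primary age and make the 6-month scores secondary. Then choose one of two courses:

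- **(a) One primary score.** Name it, with the others secondary or tested after it in a fixed order. The 338 per group, 5% and 90% then all stand for that score.
- **(b) Motor and mental as two primaries.** Test them by Holm at overall 0.05, with overall DQ secondary. Restate power at 338 per group as 84% per score at the 0.025 first step, or about 88-89% per score if both true effects are 0.25 SD. Note that 90% at the 0.025 step needs 399 per group, which the 957 randomised supply if loss is at most about 16.6%.

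The cost is wording in the protocol and analysis plan. No extra recruitment is proposed. Under (b) the stated power becomes slightly less favourable.
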